# Self-management program for patients with chronic kidney disease (SMP-CKD) in Southern China: protocol for an ambispective cohort study

**DOI:** 10.1186/s12882-022-02700-2

**Published:** 2022-03-05

**Keywords:** Chronic kidney disease, Self-management, Complex intervention, Social cognition theory, Behavior change, Cohort study

## Abstract

**Background:**

Chronic kidney disease (CKD) is a major global health problem. Short-term self-management has been considered to effect some renal and psychological endpoints. However, there are currently very few studies about self-management for CKD that a) have been scientifically designed by a theory-based framework and b) that evaluate the long-term effects and working mechanism. This study presents the rationale and design of a theory-based cohort study to explore how this self-management intervention works and its effectiveness on the Chinese CKD population.

**Methods:**

In this ambispective intervention cohort study,1,200 patients with CKD stages 1–5 will be recruited from July 2015 to July 2024 in 3 branches of Guangdong Provincial Hospital of Chinese Medicine (GPHCM) in Guangdong province, China. The patients in the self-management cohort will choose to receive an intervention that consists of education, nutrition/diet modification, lifestyle change recommendation, medication review, and psychology support based on Social Cognition Theory (SCT). The patients in the control cohort will do regular follow-ups based on the clinic rules. All the patients will be followed up for 5 years, or until the occurrence of a primary outcome. Detailed clinical, laboratory markers, nutritional status, psychological exposures and outcome questionaries will be collected semiannually in CKD stage 1–2 and trimonthly in stage 3–5 patients. The primary outcome is the occurrence of composite clinical endpoints (doubling of serum creatinine level, ESKD, loss of renal function (≥ 40% decline in GFR from baseline), death, major cardiovascular or cerebrovascular events). The main secondary outcomes include the absolute change and slope of eGFR, absolute changes of urinary protein creatinine ratio, 24-h urine proteinuria, intact parathyroid hormone level, and self-management adherence rate and quality of life from baseline to end of the study. The effectiveness of self-management will be analyzed and the association between longitudinal trajectories of self-management and renal outcomes will be evaluated.

**Discussion:**

This study aims to provide further evidence for the effectiveness of theory-based self-management in CKD patients and to improve the lives of patients with CKD by slowing progression, improving psychological well-being and overall quality of life.

**Trial registration:**

Chinese Clinical Trial Register (ChiCTR1900024633). 19 July, 2019. http://www.chictr.org.cn/showproj.aspx?proj=38378

## Background

Chronic kidney disease (CKD) is a serious global public health problem. It is reported a prevalence rate of 9.1% in global and 10.8% in Mainland China adult population [1, 2]. CKD can cause numerous complications, high morbidity, increased mortality and heavy economic burden especially progress to the end-stage kidney disease (ESKD) [3, 4]. Blood pressure control with angiotensin-converting enzyme inhibitors (ACEi) or angiotensin receptor blockers (ARB) is considered the main pharmic way to prevent CKD progression [5]. However, the traditional treatment method involves many challenges, such as insufficient knowledge acquired by patients, low participation in disease treatment decision-making, and low compliance in the treatment [6]. Hence, finding a new strategy for slow CKD progression is urgent.

Self-management, defined as the active management by individuals of their treatment, symptoms, lifestyle and the physical and psychological consequences inherent in living with a chronic condition, is an established treatment for managing CKD in recent years [7–12]. It has contributed to a paradigm shift from a paternalistic model to a more equitable and collaborative model between nephrologists and patients [13, 14]. Dietary adjustment is an important component of the self-management intervention due to disordered nutritional status and commonly appeared protein-energy wasting condition in the CKD population [15]. A scoping review revealed that diet/nutrition intervention accounts for over 60% of all list self-management topics [16]. A nutrition intervention, together with patient’s education, lifestyle change, risk factors control, psychological support, pharmacist medication review, etc. is recommended as preferred non-pharmacological alternative strategies for managing CKD patients [5].

Studies showed this emerging strategy with the function to relieve renal-related symptoms, enhance patient-centeredness and decrease patients’ concerns with depression, anxiety, self-perceived burdens [5, 15, 17–20]. However, the evidence of self-management for renal outcomes is contradictory. A randomized controlled trial (RCT) in Taiwan showed self-management may slow the reduction of estimated glomerular filtration rate (eGFR) in late-stage CKD patients within 12 months follow up, it suggested that self-management may become an effective strategy for managing CKD patients, but systematic review and meta-analysis in RCT have shown that although self-management interventions can lower 24-h urinary protein excretion, improve self-care activities and systolic blood pressure than usual care, it did not provide additional benefits for eGFR and other renal outcomes in non-dialysis patients [17–20]. While considering the median follow-up time of these studies is 13.44 months, in such a short follow-up period, it may be difficult to distinguish the real effects of self-management [20]. Furthermore, self-management is not easy to evaluate, especially in the long-term study. Adherence to the intervention plays a crucial role in the effectiveness of nonpharmacologic treatment strategies [21]. But self-management has low adherence rates, and long-term persistence is difficult [22]. During the study period, most patients’ clinical status and their participation in self-management changed dynamically, which can lead to inaccurate measures of interventions and get biased research conclusions. Therefore, its effect on thwarting the progression of CKD and other outcomes still needs further research.

What’s more, self-management interventions can be seen as complex interventions, it means not only number of and interactions between components within the interventions, but also the complexity of how the intervention works [23]. However, many studies give only a conceptual or general definition of self-management interventions, or no definition at all [18–20, 24]. When the variety among self-management interventions is not taken into account and no clear operational definition is posited, this might lead to incorrect conclusions [25, 26]. Hence, a theory-based model is preferred, it can causally link behavioral determinants, through behavior, to physiological and biochemical variables, and health outcomes [27]. This theoretical basis approach ensures interventions have a greater chance of being effective, and the reasons for these effects can be deduced [28]. However, existing research showed only 20% of studies were designed based on a theoretical framework. More knowledge about how self-management will work for CKD is still need to be studied [16].

Considering the problems and gaps above, Self-Management Program for Patients with Chronic Kidney Disease Cohort (SMP-CKD cohort), a theory-based intervention cohort study alongside a process evaluation aiming to improve the lives of patients with CKD by slowing progression and improving overall Quality of Life (QoL) will be performed. In this protocol, we present the rationale and design of this ongoing hospital-based cohort study. The objective of this cohort include i) to evaluate the long-term effectiveness of the theory-based self-management program in the Chinese CKD population; ii) to assess its longitudinal relationship to surrogate markers and renal outcomes, and; iii) to explore the working mechanism of this complex intervention.

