### Outcome measures

The primary outcome is the occurrence of composite clinical endpoints (doubling of serum creatinine level, ESKD(eGFR < 15 ml/min for CKD 1–4 patients; or dialysis for at least 30 days or kidney transplant for patients with CKD 1–5), loss of renal function(≥ 40% decline in GFR from baseline), death(from any cause), major cardiovascular or cerebrovascular events) during the 5-year follow up (shown in Table 4) [44, 45]. Those outcome data will be collected through the outcome assessment scale during each visit by reviewing the laboratory test results and the medical record in Hospital Information System (HIS).

**Table 4 Tab4:** Definition of composite clinical endpoints

Clinical events	Definition
1.A doubling of serum creatinine levels	Doubling of the serum creatinine level from baseline sustained for at least 30 days according to central laboratory assessment
2.End-stage kidney disease (ESKD)	eGFR < 15 ml/min for CKD 1–4 patients; or dialysis or kidney transplant for CKD 1–5 patients
3.Loss of renal function	≥ 40% decline in GFR from baseline
4.Death	Death from any cause
5.Major cardiovascular or cerebrovascular events	Acute heart failure, myocardial infarction, ischemic cerebral infarction or intracranial hemorrhage

The main secondary outcomes include the absolute change and slope of eGFR, absolute changes of urinary protein creatinine ratio, 24-h urine proteinuria, intact parathyroid hormone level (iPTH), and self-management adherence rates (evaluated by self-management behavior questionnaire) and quality of life. Other outcomes include serum creatinine level (SCr), blood urea nitrogen level (BUN), plasma albumin, triglyceride, cholesterol, calcium, phosphate and other Laboratory markers and cardiovascular function.

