## Statistical analysis plan

Categorical demographic and other baseline characteristics variables will be summarized by frequencies and percentages. Continuous variables will be summarized by both mean and standard deviation for data with normal distributions or median and inter-quartile range for non-normally distributed data. Either a Chi-square or Fisher’s exact test will be used to compare categorical variables between groups, while Mann–Whitney U-test or Student’s t-test will be used for continuous variables, if necessary.

The primary objective of this cohort is to evaluate the effectiveness of the self-management program, we plan to perform three separate analyses for the primary outcome. First, the incidence rate of composite endpoint events will be analyzed by the Chi-squared test. Second, time to occurrence of composite clinical endpoints will be analyzed using log rank test. The hazard ratio (HR) with 95% CI will be estimated by using the Cox proportional hazards model or competitive risk model. Third, growth mixture models and group-based trajectory models (GBTM) will be used to analyze the trajectories of exposure and outcome variables [48]. Covariates for the models will be selected based on prior knowledge and published papers. Logistic regression or Poisson regression will be used to analyze categorical outcomes. Liner mixed-effect model will be applied to the longitudinal data, such as the absolute change, and slope of eGFR and other secondary outcomes.

Even with some retention strategies, considerable missing data is expected over 5-years follow-up. The proportion of missing data will be summarized in each group and at each visit point. If there is less than 20% of data missing for the covariate data, we will perform a complete case analysis. If there is more than 20% of missing data, we will perform Little’s test and use multiple imputations under the assumption of missing is at random. Subgroup analyses will be conducted across baseline eGFR levels, demographic status and other factors, if possible. To test the credibility and robustness of the findings, several sensitivity analyses will be performed, including E-value and other advanced models [49]. Effect modification will be investigated using stratified analyses and formal tests of interaction. Mediation will be analyzed by adding the hypothesized mediators, one by one, to the confounder-adjusted models to study the extent to which they explain any association found.

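### Objective (ii) concerns renal outcomes, but the only event outcome pools renal events with death and cardiovascular events; the competing-risk model offered for it has no competing event, and follow-up stops at the first event of any type

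*Protocol article*

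**What the plan says.** **Objectives.** The Background section lists three. The first is whether the programme is effective over the long term. The second, objective (ii), is "to assess its longitudinal relationship to surrogate markers and renal outcomes". The third is how the intervention works. The Statistical analysis plan section adds: "The primary objective of this cohort is to evaluate the effectiveness of the self-management program". The limitations paragraph of the Discussion again lists surrogate markers and renal outcomes as separate items.

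**Outcomes.** Under Outcome measures, "The primary outcome is the occurrence of composite clinical endpoints". Table 4 gives five components. Three are renal: sustained doubling of creatinine, ESKD including dialysis or transplant, and a GFR decline of at least 40%. The other two are "death(from any cause), major cardiovascular or cerebrovascular events) during the 5-year follow up". The main secondary outcomes are eGFR change and slope, two measures of proteinuria, iPTH, adherence and quality of life. The other outcomes are laboratory markers and cardiovascular function. No renal-only event outcome is listed.

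**Analysis.** The Statistical analysis plan section applies a log-rank test to time to the composite, and its hazard ratio is to be "estimated by using the Cox proportional hazards model or competitive risk model". No competing event is named.

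**Follow-up.** The abstract and the section Study design and study population both end a patient's follow-up at the first primary-outcome event if that comes before five years.

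**The concern.** Three features of the plan combine.

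- A study that wants to speak about renal outcomes, and about slowing CKD progression, has no event outcome made up of renal events alone. An effect confined to the kidney is diluted in the composite, and an effect on the composite need not be renal.
- The plan names a competing-risk model but attaches it to the one endpoint where it can do nothing. The endpoint where it would matter, renal events with death competing, is not defined.
- Follow-up stops at the first event of any type. A patient with a non-fatal infarction or stroke contributes no later creatinine doubling, ESKD or eGFR values. A renal analysis added after the fact could not fully recover them.

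At stake is whether the study can estimate an effect on renal events at all.

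**Working it through.** **1. The plan's own figure.** The Sample size calculation section gives 30 variables and at least 10 endpoints per variable: 30 × 10 = 300 events, which reproduces. With 1,200 patients, 60 per 1,000 person-years and 5 years, first events without loss are 1,200 × (1 − exp(−0.06 × 5)) = 311, close to 300. The rate and the 300 events both refer to the whole composite, so the plan gives no renal event count.

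**2. Is there a competing event?** An event competes only if it prevents the outcome from occurring. Candidates set against Table 4:

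| Candidate | Status in Table 4 |
|---|---|
| Death from any cause | Component 4 |
| Dialysis | Within component 2 |
| Kidney transplant | Within component 2 |

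None is left outside. With no competing cause, the cumulative incidence is the sum of S(t−) × d/n over event times, where S is the Kaplan–Meier curve of the event itself, and that sum is 1 − S. In a simulated cohort of 1,200 (hazard 0.06 a year, random loss), both estimators gave 0.2580. The Fine–Gray risk set keeps patients who have had a competing event. There are none, so the model is the Cox model.

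**3. Dilution in the composite (illustration).** The renal share s is not in the document and is assumed. With a renal HR of 0.70 and a non-renal HR of 1.0, composite HR ≈ s × 0.70 + (1 − s) × 1.0:

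- s = 0.6: 0.82
- s = 0.7: 0.79
- s = 0.8: 0.76

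**4. Events left for a renal-only outcome.** Renal events = 300 × s. Events per variable = renal events / 30. Power by Schoenfeld = Φ(√(events/4) × |ln HR| − 1.96). Assumed: HR 0.70, two-sided 0.05 and cohorts of equal size; none of these is stated in the document.

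| s | Renal events | Per variable | Power at HR 0.70 |
|---|---|---|---|
| 0.5 | 150 | 5 | 59% |
| 0.7 | 210 | 7 | 73% |
| 0.9 | 270 | 9 | 83% |

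With s = 0.7 and an effect confined to the kidney, the composite has 300 events at HR 0.79: √75 × 0.2357 − 1.96 = 0.08, or 53% power. The renal-only outcome has 210 events at HR 0.70: √52.5 × 0.3567 − 1.96 = 0.62, or 73%. In that scenario fewer events do not mean less power. If the effect were equal on all components, the composite would do better (87% with 300 events at HR 0.70).

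**The case against.** **The composite fits the primary objective.** A reader might infer that the primary outcome contradicts what the study set out to do. It does not. The primary objective is effectiveness in general, and a composite of renal, cardiovascular and fatal events is compatible with it. The renal wording belongs to objective (ii), which speaks of a longitudinal relationship. This stands.

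**Objective (ii) already has outcomes and analyses.** eGFR slope is a direct measure of progression, and linear mixed models and trajectory models are planned. This stands in part. The protocol itself separates surrogate markers from renal outcomes, so the markers alone do not cover the objective, and the eGFR series is also cut short by the stopping rule.

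**A renal-only secondary outcome could be left to a fuller document.** The outcome lists are not stated to be exhaustive, so its absence alone would be a weak point. What the article does state is the misplaced model and the end of follow-up at the first event. On the charitable reading that the competing-risk model was meant for renal events, the endpoint it needs is still not listed.

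**The competing-risk wording does no numerical harm.** True: the estimates for the composite would be the same. The loss is that the model is not assigned to an endpoint where it would tell something.

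**Self-selection.** Controls are patients who decline the programme, so a reader might infer that a favourable composite would merely reflect fewer deaths and cardiovascular events among healthier choosers. The documents give no component mix and no ground for supposing that such choosers have the same renal prognosis. That is confounding. The Discussion acknowledges it, adjusted models and E-values are planned against it, and a renal-only outcome would not remove it.

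**Conclusion.** The point holds in this form: objective (ii) is served by markers but by no renal event outcome; the competing-risk option is attached to an endpoint without a competing event; and the follow-up rule would discard renal information after a non-fatal cardiovascular event. The last two follow from the text and need no assumption.

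The size of the dilution does rest on assumptions. With a renal share of 60–80% and an effect confined to the kidney, a renal HR of 0.70 appears as 0.82 to 0.76. The true share is unknown.

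No figure in the document is shown to be wrong, and the primary analysis is not invalidated. This should be changed, and early, because follow-up that has been stopped may not be recoverable later.

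**What to change.** - Add a secondary outcome: time to first renal event (components 1–3 of Table 4). Analyse it by cause-specific Cox together with the competing-risk model already named. The competing event is death from any cause before a renal event, which needs no cause-of-death classification.
- Use plain Cox for the full composite and delete the competing-risk option there.
- Continue collecting renal data after a non-fatal cardiovascular or cerebrovascular event, through the clinic visits and hospital records already in use, and reword the end-of-follow-up statements to match.
- Report the components separately, and base statements about slowing CKD on the renal outcome and eGFR slope.

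**Cost.** One extra analysis, changes of wording, and some continued data collection. The renal outcome has fewer events: 150–270 of 300 at an assumed share of 50–90%, or 5–9 per variable for 30 variables. That is below the plan's own minimum of 10, so the renal model needs fewer covariates or must accept a wider interval. Confounding by self-selection remains and has to be handled separately.

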## Methods

### Study design and study population

An ambispective cohort study will be conducted in the department of nephrology at the three branches of Guangdong Provincial Hospital of Chinese Medicine (GPHCM) in Guangdong province, China. Two branches are located in different Districts in Guangzhou city (Yuexiu and Fangcun District) and one in Zhuhai city. The study population includes all CKD 1–5 patients (speak Cantonese or Mandarin) attending the CKD consultation outpatient clinic in GPHCM from July 2015 to July 2024. Of 200 CKD patients were already registered in the retrospective cohort from July 2015 to July 2019 and they will keep following in the prospective cohort. Beginning in August 2019, a prospective cohort will be built on. All the patients will be followed for at least 5 years, or until the occurrence of a primary outcome.

CKD is defined by a glomerular filtration rate (GFR) < 60 mL/min/1.73 m2 or markers of kidney damage, or both, of at least 3 months duration [5]. GFR is calculated by CKD-EPI equation, and CKD staging will use the Kidney Disease Outcomes Quality Initiative (KDOQI) definition [29]. Patients are eligible for inclusion if they are Chinese, aged 18 to 80 years, have CKD (Stages 1–5), and give a written signed informed consent. Exclusion criteria for the study are psychosis or unable to cooperate with clinical staff for other reasons and have a history of dialysis or renal transplant.

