### Intervention design

Social Cognition Theory (SCT) will be applied to design a theory-based complex intervention. According to SCT, motivational enhancements can ultimately lead to behavior modification. It can help the individual modify their behaviors, and then elevate the individual’s perceived self-efficacy and outcome expectations [30]. The Behavior Change Technique Taxonomy v1 will be used to specify the self-management intervention functions and behavior change techniques [31].

Self-management interventions components will be selected by reviewing existing epidemiological evidence, consulting clinical psychologists, sociologist, epidemiologists, and holding group meetings. The components of this complex intervention include education, nutrition/diet modification, lifestyle change recommendation, medication review and psychology support. A multidisciplinary team consisting of nephrologists, nurses, dietitians, and postgraduate students will be in charge of the delivery of all the interventions. All the team members will participate in a 1-day workshop to standardize their delivery.

The education will entail a 1.5-h integrated slide-lecture, delivered by nephrologists and dietitians trimonthly involving general CKD knowledge, dietary management, healthy lifestyle, pharmacological regimens and Chinese herbal medicine instructions. Cooking courses will be offered semiannually for 2 h a session with different topics (macro-and micro-nutrients intake and restriction, label reading, eating out, et al.), provided by dietitians and nurses. All the courses will be taught in Cantonese or Mandarin to accommodate the main languages spoken in the Guangdong Province.

After assessing baseline anthropometric parameters and biochemical findings, patients will receive face-to-face dietary counseling from a dietitian includes the protein, caloric, potassium, phosphorus, sodium intake recommendations. Before each follow-up/clinic visit, they will be asked to fill a diet diary to record all foods and beverages consumed for 72 h, in succession two weekdays and one weekend day, then dietitian will assess their compliance by analyzing the diary data and offer new individualized dietary prescriptions. All these recommendations and prescriptions are based on the Chinese guideline [32].

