## Measures

### Exposure measures

The details of the data collection are shown in Table 1. Social-demographic and clinical data will be collected only in prospective cohort by a predetermined questionnaire during the initial visit. Physical examination and laboratory markers will be collected trimonthly in patients with CKD 3–5 and semiannually in patients with CKD 1–2.

The nutritional parameters will be evaluated by 1) a validated daily diet record form recording all foods and beverages consumed for 72 h, in succession two weekdays and one weekend day before the 24-h urine sample is collected. Trained staff will teach all patients how to keep proper records in their diet logs. These dietary data will be converted into daily nutrient intakes by using the “Chinese food composition list, 2nd edition” [33]. 2) Inbody-770 and tool measuring for anthropometric parameters and Medgraphics Ultima CCM for metabolic characteristics [34, 35]. 3) Patient-Generated Subjective Global Assessment (PG-SGA) for symptoms, metabolic stress and nutritional status [36].

A 11-item self-management behavior questionnaire developed by our team will be used to measure the self-management compliance. Patients-reported outcomes (PROMs) will be used to identify lifestyle factors, self-efficacy, psychological status and quality of life. A cognitive questionnaire will be given to determine patients’ cognitive levels so that the nursing group can schedule receptive and individualized courses [37]. Social support score will be collected by the Social Support Rating Scale (SSRS), self-efficacy score will be assessed by General Self-Efficacy Scale (GSES), and patient and doctor relationship will be measured by a developed Patient-Doctor Relationship Questionnaire (PDRQ-13) [38–40]. Patients’ other lifestyle factors (e.g., sleep and physical activity) will be evaluated by the Pittsburgh Sleep Quality Index (PSQI), and the International Physical Activity Questionnaire (IPAQ) [41, 42]. The Short Form Healthy Survey Questionnaire (SF-12) will be used to measure CKD patients’ quality of life [43]. All above self-reported questionnaires are validated in Chinese population.

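### A diet-induced fall in creatinine generation in the programme cohort could pass for slower CKD progression, and no stated analysis separates the two

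*Protocol article*

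**What the plan says.** All references are to the Protocol article.

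- **GFR method** (Study design and study population): "GFR is calculated by CKD-EPI equation, and CKD staging will use the Kidney Disease Outcomes Quality Initiative (KDOQI) definition". The marker entering the equation (creatinine, cystatin C or both) is not named.
- **Laboratory routes to the primary endpoint** (Outcome measures, Table 4): "Doubling of the serum creatinine level from baseline sustained for at least 30 days according to central laboratory assessment"; "eGFR < 15 ml/min for CKD 1–4 patients; or dialysis or kidney transplant for CKD 1–5 patients"; "≥ 40% decline in GFR from baseline". Death and major cardiovascular or cerebrovascular events complete the composite.
- **Secondary outcomes** (Outcome measures): "The main secondary outcomes include the absolute change and slope of eGFR", followed by proteinuria, parathyroid hormone, adherence and quality of life.
- **Intervention** (Intervention design): once baseline anthropometry and biochemistry have been assessed, "patients will receive face-to-face dietary counseling from a dietitian includes the protein, caloric, potassium, phosphorus, sodium intake recommendations". Individual dietary prescriptions are renewed after diary review at follow-up visits.
- **Controls** (Abstract; Screening and Enrollment): regular follow-up under the clinic's rules.
- **24-h urine** (Exposure measures): the 72-h diet record covers, "in succession two weekdays and one weekend day before the 24-h urine sample is collected". 24-h proteinuria is a main secondary outcome.
- **Safeguards**: the Statistical analysis plan section names the E-value and unspecified advanced models as sensitivity analyses. The Discussion rates the misclassification risk for renal outcomes as low.

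**The concern.** Serum creatinine reflects both filtration and creatinine generation, and generation depends on meat or protein intake and on muscle mass. The programme acts on diet, in one cohort, after the baseline value has been taken. If it lowers generation, creatinine falls and creatinine-based eGFR rises while true GFR stays the same. Fewer programme patients then cross the creatinine and eGFR thresholds at a given true loss.

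The stated safeguards do not address this. Baseline covariates cannot remove a shift that arises after baseline. The E-value concerns unmeasured confounding, not a treatment effect on the measuring instrument. At stake is the first objective, long-term effectiveness, and with it any claim that the programme slows progression.

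**Working it through.** **1. The plan's own figure.** Sample size calculation: 30 variables × 10 events = 300 events, which reproduces exactly. At 60/1,000 person-years, 1,200 patients over 5 years give 1,200 × (1 − exp(−0.06 × 5)) = 311 events, or 1,200 × 5 × 0.06 = 360 with constant person-time. This neither supports nor weakens the point; 300 is used below only as the number of events.

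**2. Assumptions.** The protocol gives no direction or size for the protein change, so these are assumed. At steady state, serum creatinine is proportional to generation/true GFR. Creatinine-based eGFR is proportional to creatinine^(−a), with a = 1.0 to 1.2. Generation falls by g = 3%, 5% or 10% after baseline, in the programme cohort only.

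**3. Shift in the thresholds.**
- Apparent eGFR gain at unchanged GFR: (1 − g)^(−a) − 1
- True loss needed for doubling: 1 − 0.5(1 − g)
- True loss needed for the 40% criterion: 1 − (1 − g) × 0.6^(1/a)

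| g | eGFR gain (a = 1.2) | Doubling | 40% criterion, a = 1.2 | 40% criterion, a = 1.0 |
|---|---|---|---|---|
| 0 | 0 | 50% | 34.7% | 40% |
| 3% | 3.7% | 51.5% | 36.6% | 41.8% |
| 5% | 6.3% | 52.5% | 37.9% | 43.0% |
| 10% | 13.5% | 55.0% | 41.2% | 46.0% |

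**4. Effect on the composite.** A null simulation gave both cohorts the same true GFR course and the same rate of non-laboratory events. Assumed: baseline eGFR 20 to 110; mean loss 1.5 or 2.5 mL/min/1.73 m² per year (SD 2.5 or 3.0); non-laboratory events 10 or 20 per 1,000 person-years; quarterly visits; 5% measurement noise; laboratory events confirmed at the next visit; a = 1.2; full adherence for five years. Control composite rates were 42 to 78 per 1,000 person-years, which brackets the plan's 60. The last column uses Schoenfeld's formula with 300 events, two-sided 0.05 and 1:1 allocation, all but the 300 assumed.

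| g | Spurious composite rate ratio | Chance of a false benefit |
|---|---|---|
| 3% | 0.92–0.94 | 8–10% |
| 5% | 0.88–0.90 | 14–20% |
| 10% | 0.79–0.83 | 38–52% |

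**5. Waning adherence.** A second simulation, of the 40% criterion alone (identical true loss averaging 4–6% per year), gives larger ratios because no non-laboratory events dilute them. It shows how far the result depends on persistence.

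| Assumed pattern | g = 3% | g = 5% | g = 10% |
|---|---|---|---|
| Full shift for 5 years | 0.84–0.88 | 0.74–0.80 | 0.53–0.62 |
| Half the patients adhere fully | 0.92–0.94 | 0.87–0.90 | 0.76–0.81 |
| Shift halves every 2 years | 0.97–0.98 | 0.95–0.96 | 0.90–0.92 |
| Shift halves every year | 0.98–0.99 | 0.98–0.99 | 0.98–0.99 |

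**6. Slope.** A one-off step after baseline moves a straight-line slope over 5 years by 2.5/Σ(t − 2.5)² of the step per year. That is 2.5/48.125 = 0.052 with quarterly visits and 2.5/27.5 = 0.091 with half-yearly visits. At eGFR 60 and g = 10% the step is 60 × 0.135 = 8.1, so the slope moves by about 0.4 to 0.7 mL/min/1.73 m² per year. The absolute change carries the whole 8.1.

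**The case against.** The case on the other side is substantial, and much of it stands.

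- **Direction is not stated.** The Background partly justifies the dietary component by protein-energy wasting, so some patients may be advised to eat more. The guideline behind the prescriptions is not at hand, and the dietary content of the controls' usual care is not described. This stands: the bias is possible, not shown.
- **The marker is inferred.** Only the doubling criterion names serum creatinine. Table 1 is not shown and could list another marker, though no outcome definition in the text uses one.
- **Persistence.** The Background and Discussion expect low and declining adherence. This stands and moves the ratios towards 1.
- **Some data already help.** Body composition, nutritional assessment and diet diaries are planned. They could support an interpretation, but no stated analysis links them to the renal endpoints.
- **Detail may sit in an unseen analysis plan.** Fair for model details. But the article fixes the endpoints and itself calls misclassification risk low.

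A reader might infer more than the documents support:

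- That every laboratory outcome is change from a pre-diet value. eGFR below 15 is an absolute threshold, and the slope comes from a mixed model.
- That the 24-h urine serves only proteinuria. The text merely states no use for creatinine excretion or clearance.
- That 0.53–0.62 applies to the primary endpoint. It covers the 40% decline alone, at a 10% fall with full five-year adherence.
- That events should be re-referenced to the first post-baseline visit. If the shift fades, that reference is inflated and the return counts as decline, which biases against the programme.

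**Conclusion.** The concern holds as a limit on interpretation. The intervention can act on the marker behind the laboratory endpoints, after baseline and in the cohort that receives the dietary counselling, and no stated analysis would distinguish this from slower progression.

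Under an assumed, fully sustained 3% to 10% fall in generation, the spurious composite rate ratio is roughly 0.94 to 0.79. It is nearer 1 if adherence wanes. Absolute eGFR change and the threshold events are most exposed, the slope less so unless the fall in generation is progressive. Dialysis, transplant, death and cardiovascular or cerebrovascular events are not defined by creatinine and are unaffected.

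It would go too far to say that a renal benefit in this study would be an artefact, or that the programme will lower creatinine generation. The documents give neither direction nor amount.

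**What to change.** 1. State which marker or markers enter the CKD-EPI equation.
2. Measure creatinine in the 24-h urine already collected, and compare the change in 24-h creatinine excretion between cohorts. Report creatinine clearance as a supportive measure: at steady state, lower generation reduces excretion and serum creatinine together and leaves clearance unchanged.
3. Pre-specify a sensitivity analysis of the primary endpoint limited to dialysis, transplant, death and major cardiovascular or cerebrovascular events.
4. Qualify the Discussion's statement on low misclassification risk, and say that a renal benefit will be read cautiously if creatinine excretion falls more in the programme cohort.

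The slope from the first post-baseline visit may be shown beside the total slope, as supportive only. Neither re-referencing events to that visit nor making a claim conditional on agreement with clearance is advised. Nothing here bears on the content of the dietary advice.

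The cost is a creatinine assay on existing samples, some wording and analysis time. This assumes that both cohorts give 24-h urine, as a between-cohort comparison of 24-h proteinuria would need. The drawbacks are that 24-h collections are noisy and that the creatinine-independent analysis has fewer events, so it can support or question the main result but not replace it.
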